## Abstract

**Background:**

Symptomatic hemorrhoids are one of the most common anorectal disorders. Many surgeons use tamponades after open hemorrhoidectomy to manage postoperative bleeding. The question of whether a tamponade is necessary and beneficial after hemorrhoidectomy has not yet been conclusively answered. A previously conducted single-center pilot trial included 100 patients after Milligan–Morgan hemorrhoidectomy. The data indicated that insertion of an anal tamponade after hemorrhoidectomy does not reduce postoperative bleeding but causes significantly more pain. The findings of this pilot trial are now to be verified by means of a multicenter randomized clinical study called NoTamp.

**Methods:**

We plan to include 953 patients after Milligan-Morgan or Parks hemorrhoidectomy in the NoTamp study. The aim is to demonstrate that using no tamponade dressing after open hemorrhoidectomy is not inferior to using tamponades with respect to postoperative bleeding, and that the patients report less pain. Primary endpoints of the trial are the maximum postoperative pain within 48 h and the incidence of severe postoperative bleeding that requires surgical revision within 7 days after the surgical procedure. Secondary endpoints of the study are the use of analgesics in the postoperative course, the lowest hemoglobin documented within 7 days, quality of life and patient satisfaction. Safety analysis includes all adverse and serious adverse events in relation to the study treatment. Further information can be found in the registration at the German Registry of Clinical Studies (DRKS00011590) and on the study webpage (https://notamp.de/en-GB/trial/main/setLocale/en_GB/). The study is financed by the HELIOS research funding.

**Discussion:**

The study received full ethics committee approval. The first patient was enrolled on 3 May 2017. This trial will finally answer the question whether the insertion of a tamponade after open hemorrhoidectomy is necessary and beneficial.

**Trial registration:**

German Clinical Trials Register (Deutsches Register Klinischer Studien (DRKS), DRKS00011590. Registered on 12 April 2017.

## Background

Symptomatic hemorrhoids are one of the most common anorectal disorders [1–3]. The exact incidence of hemorrhoid disease is difficult to quantify and published epidemiologic data are rather old and rare. The prevalence is approximately 4% in the United States of America, [4] with presentation peaking between the ages of 45 and 65 years. Since the second half of the twentieth century, there seems to have been an unexplained decrease in the prevalence of symptomatic hemorrhoid disease in both the USA and England [5]. It is estimated that approximately 50% of all Germans develop symptomatic hemorrhoids during their lifetime and some authors even suggest that up to 70% of the adult population is affected by hemorrhoids [6]. However, these numbers are not based on epidemiological data, but are estimated by experts [7]. Symptomatic hemorrhoids are very common in both men and women. About half of all people aged 50 years have symptomatic hemorrhoid disease. About 40% of individuals with hemorrhoids are asymptomatic [1].

Symptomatic hemorrhoid disease has a large impact on quality of life, and can be managed with a multitude of surgical and nonsurgical treatments [8]. Treatment options comprise conservative and surgical therapy applied according to individual patient and clinical factors [9]. Continued symptoms despite conservative or minimally invasive measures usually require surgical intervention, and surgery is the initial treatment of choice in patients with symptomatic grade IV hemorrhoids or those with strangulated internal hemorrhoids [8]. It may also be required for symptomatic grade III hemorrhoids and in patients who present with thrombosed hemorrhoids.

In recent years a variety of surgical procedures has become available for treating symptomatic hemorrhoids, but high (Parks) or low (Milligan-Morgan) ligation with excision is still one of the common performed surgeries. The most commonly used method for treating third-degree and fourth-degree enlarged hemorrhoids is still Milligan-Morgan’s surgical procedure [2, 3, 10–13]. The open hemorrhoidectomy is often the preferred approach to surgically treat severe acute gangrenous hemorrhoids where tissue edema and necrosis preclude closure of the mucosa [14].

Hemorrhoidectomy is generally performed as an inpatient procedure [12], as it may be associated with significant postoperative complications like pain, bleeding, pruritus and mucus production. The occurrence of bleeding is often associated with the first passage of hard stool after surgery. Early bleeding can also result from inadequate thrombus formation. Postoperative bleeding can be a serious complication that may range from causing discomfort to being potentially life-threatening. Postoperative bleeding may occur in 2–6% of the cases [15–17], with early bleeding being more common than late bleeding [18, 19].

Depending on the extent of dissection and due to the presence of incisions below the dentate line, postoperative pain can be severe, and may delay return to normal activities for several weeks. Pain can usually be managed with oral analgesics, avoidance of constipation, and sitting in a bath.

Postoperative bleeding may occur in 1–2% of patients 1 week after surgery as a result of eschar separation and is usually self-limited [20]. Patients requiring a combination of aspirin and thienopyridine derivatives (e.g., clopidogrel) have a heightened risk of bleeding [21].

In order to avoid postoperative bleeding as well as pain after hemorrhoidectomy, surgical techniques and instruments have been improved and further developed [22]. Additionally, researchers investigated stool softeners and oral administration of metronidazole [12].

In order to control postsurgical bleeding, many surgeons insert an anal tampon, but little scientific attention has been paid to the necessity of local dressings after hemorrhoidectomy. Benefit and possible disadvantages (e.g. pain) of the tamponades are under discussion.

Two randomized studies evaluated the effects of anal tampons after hemorrhoidectomy. Myles et al. compared a simple, non-adherent wound pad with a gelatin sponge plug [23]. Ingram et al. performed a study comparing a calcium alginate dressing with standard gauze packing after hemorrhoidectomy [24]. Both studies focused on the effects of different types of tamponades on the severity of pain and bleeding. Nevertheless, the fundamental question of whether tamponade is really necessary and beneficial after hemorrhoidectomy has never been answered in a comparative study.

Within a previously conducted single-center randomized controlled pilot study performed by the same study group (DRKS-ID: DRKS00004568) 100 patients surgically treated with Milligan-Morgan hemorrhoidectomy have been randomized to be treated either with a postoperative anal tampon (48 patients) or without (52 patients) [25]. The primary endpoint of the study, maximum pain intensity (0–10), has been shown to be significantly lower in patients without tamponade (4.2) than in the group with tamponade dressing after surgery [1, 6] (*p* = 0.001). Complications occurred in 7 patients (15%) in the group with tamponade and in 11 patients in the group without tamponade (21%) (*p* = 0.444), whereas the number of patients with severe anal bleeding was small in both groups (*n* = 2 with tamponade and *n* = 5 without tamponade). Bandage changes were required less often in the group treated without tamponade (*p* = 0.013). The average length of hospital stay was 4 days in both groups.

The results of the pilot study indicate that using tamponade after hemorrhoidectomy significantly increases postoperative pain but has no value in avoiding postoperative bleeding. With the exception of patients on anticoagulants, who have a heightened risk of severe postoperative bleeding, the use of anal tamponade dressings after hemorrhoidectomy seems not to be necessary in routine care.

The results of the pilot study should now be verified by means of a multicenter randomized clinical trial (RCT). This multicenter RCT aims to prove that the established postoperative routine of using tamponade after hemorrhoidectomy has no additional benefit in avoiding postoperative bleeding but leads to significantly more postoperative pain. The NoTamp-study aims to create sufficient evidence base for decision-making on the necessity of using tamponade dressings after hemorrhoidectomy.

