## Methods/design

### Aim of the study

The primary aim of the study is to prove that in routine clinical practice, treating patients without a tamponade dressing after hemorrhoidectomy results in a lower pain burden, and is non-inferior to the use of tamponade in terms of the incidence of severe postoperative bleeding requiring surgical revision. 

Secondary aims are to assess all patients in the group without primary tamponade dressing after surgery who needed emergency tamponade, and to compare differences between the study groups in preoperative and postoperative hemoglobin values and the use of pain medications. Quality of life and patient satisfaction will also be compared between the two treatment groups.

The safety analysis aims to compare the number of adverse events (AE) and serious adverse events (SAE) in the two study groups in order to make a statement on the potential risk to patients without a tamponade dressing after hemorrhoidectomy.

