In order to address the primary aim of the study to prove that treating patients without a tamponade dressing after hemorrhoidectomy results in a lower pain burden while the incidence of bleeding requiring surgical revision is no greater than in the patients treated with tamponade (non-inferiority), the primary outcome variables will be examined in terms of an a priori ordered hypothesis at a level of significance of 0.05. Pain values will be described by the mean (SD) and median (IQR). The last observation carried forward (LOCF) method will be used to replace missing values for pain, but only if at least one documentation of postoperative pain is available. Differences in pain will be analyzed using the non-parametric U test (two-sided; alpha = 0.05). If significantly lower pain levels are detected in the treatment arm without tamponade, non-inferiority in the bleeding rate will be also be analyzed at the 5% significance level. Alpha error correction is not required [27]. The incidence of postoperative bleeding needing revision (bleeding rate) will be determined in both treatment arms and will be tested for non-inferiority by calculating the 90% confidence interval (CI) (one-sided hypothesis), with a rate of bleeding two times higher considered acceptable, whereas a bleeding rate three times higher will no longer be considered non-inferior. This rate difference (together with the 90% CI margins) will be considered in relation to the observed revision rate in the control arm. This gives the estimator for the relative increase together with the confidence margins. If the upper limit of this relative increase exceeds 3, then a threefold increase is still possible and non-inferiority is rejected. If the upper limit of this relative increase is < 3, non-inferiority is assumed (with an error rate of 5%). In the unexpected case that the revision rate in the control group is rather low (< 2%) or even 0%, the relative increase will not be calculated. In this case, only the revision rates in the treatment groups are reported (with the 95% CI). The number of patients requiring tamponade in the postoperative course in the group that did not receive primary tamponade after surgery will be presented with the 95% CI.

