Based on the results of the single-center pilot study that demonstrated significant pain reduction (first primary outcome) without tamponade, it can be assumed with great probability that an advantage can also be demonstrated in this much larger multicenter study (first hypothesis). For the second primary outcome based on the results of the pilot study and the international literature it is predicted that 4% of the patients will need surgical revision with tamponade due to severe postoperative bleeding in the treatment group (96% estimated success rate in the control group).

In the intervention group without tamponade a slightly higher rate of bleeding needing surgical revision of ca. 8% is expected. The bleeding rate was 10% in 52 cases included in the pilot study. Therefore, the clinically acceptable and justified limit for non-inferiority is set at 12%, or 8% higher than in the control group with tamponade (8% non-inferiority limit).

Based on these assumptions, the sample size is 433 per group, or 866 patients in total. For study enrollment, assuming a maximum 10% rate of loss to follow up, 953 patients are required. The power was set at 80% in all calculations. Detailed procedures for executing the statistical analysis of the primary and secondary variables and other data will be provided in a statistical analysis plan.

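### Two passages state the bleeding conclusion as no benefit or no greater rate, which is stronger than the non-inferiority test can support when the trial is planned on revision bleeding doubling

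*Protocol article*

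**What the plan says.** The protocol article words the bleeding objective in three ways.

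- Background: the trial aims to prove that the routine of "using tamponade after hemorrhoidectomy has no additional benefit in avoiding postoperative bleeding but leads to significantly more postoperative pain".
- Statistical analysis and power calculation: the primary aim is restated as showing that "the incidence of bleeding requiring surgical revision is no greater than in the patients treated with tamponade (non-inferiority", with the bracketed term offered as its equivalent.
- Aim of the study: treatment without a tamponade "is non-inferior to the use of tamponade in terms of the incidence of severe postoperative bleeding requiring surgical revision". The abstract's Methods and the Design section also speak of non-inferiority.

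The planning assumptions are in the statistics section. For control, "4% of the patients will need surgical revision with tamponade due to severe postoperative bleeding". For the other arm, "In the intervention group without tamponade a slightly higher rate of bleeding needing surgical revision of ca. 8% is expected". The "limit for non-inferiority is set at 12%, or 8% higher than in the control group with tamponade (8% non-inferiority limit".

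The decision rule in the same section is relative and uses a 90% CI: "If the upper limit of this relative increase is < 3, non-inferiority is assumed (with an error rate of 5" per cent). The section also calls a twofold rate acceptable and a threefold rate not.

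**The concern.** A non-inferiority test answers one question: is the excess smaller than the margin? It cannot show that the excess is zero, and here the plan expects it not to be. Going from 4% to 8% means that tamponade is assumed to halve revisions for bleeding. A design built to succeed when that benefit is real cannot prove that the benefit is absent.

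The stronger wording could carry through to the conclusion. The Background already reads a pilot with 5 of 52 severe bleeds without tamponade and 2 of 48 with it as showing that tamponade has no value against bleeding. The sample size paragraph uses the same pilot to expect more bleeding without it. Surgeons deciding whether to drop tamponades need the pain gain weighed against any real excess of re-operations, and a conclusion of no benefit would hide that trade.

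**Working it through.** **Inputs** (Statistical analysis and power calculation; 1:1 allocation from Design): control rate 4%, rate without tamponade 8%, margin 8 points, one-sided 5% (90% CI), power 80%, 433 per arm.

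**1. The plan's own figure.** With unpooled variance,

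n = (1.645 + 0.842)² × (0.04×0.96 + 0.08×0.92) / (0.08 − 0.04)² = 6.18 × 0.112 / 0.0016 ≈ 433 per arm.

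This reproduces the stated size, so the trial is powered on a true doubling.

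**2. Where both statements hold at once.** SE = √(0.112 / 433) = 0.01608.

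- Non-inferior: observed difference below 0.08 − 1.645 × 0.01608 = 5.35 points.
- 95% CI wholly above 0: observed difference above 1.96 × 0.01608 = 3.15 points.

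An observed excess between about 3.15 and 5.35 points meets both.

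**3. Probability at the planning rates.**

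- Normal approximation: P(non-inferior) = 80.0%, P(CI above 0) = 70.1%, P(both) = 50.1%.
- Exact enumeration of two binomials, 433 per arm: 79.5%, 70.7% and 50.3%. So 0.503 / 0.795 = 63% of the non-inferior trials would also show significantly more revision bleeding.
- With Fisher's exact test for the excess, P(both) = 45%.

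**4. Sensitivity to the true rate** (8-point margin, control 4%, 433 per arm, exact): P(both) is about 26% if the true rate without tamponade is 6%, and about 2% if the rates are equal.

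**5. Sensitivity to the decision rule** (planning rates, control rate at least 2% as the plan requires). Let U be the upper 90% limit of the difference and c the observed control rate.

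- 1 + U/c < 3: P(both) = 37%.
- U/c < 3: P(both) = 62%.
- A log risk-ratio interval with upper limit below 3: 12.5%. The article does not describe this calculation; it is shown only for range.

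**6. One data set.** 39 of 433 revisions without tamponade (9.01%) against 17 of 433 with it (3.93%):

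- Difference 5.08 points, SE 1.66.
- 90% CI +2.3 to +7.8, so non-inferior on 8 points.
- 95% CI +1.8 to +8.3, so an excess is shown.
- 1 / 0.0508 ≈ 20, so about one extra revision per 20 patients.

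On the stricter direct reading this example passes narrowly (1 + 7.82/3.93 = 2.99). On a log risk-ratio interval it fails (upper limit 3.65).

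All these figures take the pain comparison, which comes first in the ordered testing, as passed. The plan regards that as very probable.

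**The case against.** The strongest reply is that the formal aim is already right. The Aim, the abstract and the Design section say non-inferior, the statistics passage carries non-inferiority in brackets, and the same section openly calls a doubled rate acceptable. The expected 8% is stated plainly, and planning on a somewhat worse true rate is conservative. A result that is both non-inferior and significantly worse is possible under any margin. All of this stands. It makes the point one of aligning the wording, and the design need not change.

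Three stronger readings are tempting, and the article does not support them.

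- *That the plan never looks at whether the difference excludes zero.* It carries both 90% limits of the difference, so in the example above an interval of +2.3 to +7.8 would be in the planned output. It also puts tamponade use into a logistic regression for severe bleeding and compares adverse events between arms. The regression is adjusted and based on use, and the adverse event comparison is not confined to the primary bleeding event. Neither replaces the randomised contrast, but they are not nothing.
- *That the trial will report no benefit as proven.* No passage fixes that as the success statement; the decision rule itself says only that non-inferiority is assumed.
- *That half of all such trials would give this result.* That holds at the planning rates and the 8-point margin only.

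Leaving details to the SAP does not remove the point, because the objection is to wording that is present and that conflicts with the stated aim.

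**Conclusion.** The point holds as a mismatch of claims. The Background sentence and the restated aim in the statistics section promise more than the test can deliver, and they disagree with the abstract, the aim and the design section. At 4% against 8%, 433 per arm and an 8-point margin, about half of trials would be non-inferior with a 95% CI wholly above 0. The range is 37% to 62% on the two direct readings of the relative rule, and with the 8-point margin the figure falls to about 26% at a true 6% and 2% at equal rates. The two-sided comparison behind these figures is not a planned test; it is what the same data would show a reader. The mismatch in wording does not depend on any of these probabilities. What is missing is a rule that ties the conclusion to the interval.

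**What to change.** Align the Background sentence and the restated aim in the statistics section with Aim of the study, so that success means only that the excess in bleeding needing revision is below the pre-set margin.

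Report the two-sided 95% CI for the randomised difference beside the non-inferiority test. If its lower limit is above 0, state that revision bleeding is increased, set this next to the pain result, and do not claim no benefit or a rate that is no greater.

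The cost is a few words and one interval from data already collected. Sample size and conduct are unchanged. The downside is a less favourable claim. Adding a number needed to harm would be a reporting preference and is not part of this point.

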## Methods/design

### Aim of the study

The primary aim of the study is to prove that in routine clinical practice, treating patients without a tamponade dressing after hemorrhoidectomy results in a lower pain burden, and is non-inferior to the use of tamponade in terms of the incidence of severe postoperative bleeding requiring surgical revision. 

Secondary aims are to assess all patients in the group without primary tamponade dressing after surgery who needed emergency tamponade, and to compare differences between the study groups in preoperative and postoperative hemoglobin values and the use of pain medications. Quality of life and patient satisfaction will also be compared between the two treatment groups.

The safety analysis aims to compare the number of adverse events (AE) and serious adverse events (SAE) in the two study groups in order to make a statement on the potential risk to patients without a tamponade dressing after hemorrhoidectomy.

### Design

The NoTamp study is designed as a German national, multicenter, randomized controlled clinical non-inferiority trial. Participants are randomly allocated in a 1:1 ratio to each treatment group. Randomization will be stratified per study site. Allocation to treatment groups will be performed using a centralized web-based tool. Randomization is recommended to be performed at the earliest 12 h before the start of surgery. The patient will not be informed about the result of randomization before surgery. The duration of the clinical trial for each randomized patient is 7 days. There will be no blinding of participants, physicians, nurses or outcome assessors. No interim analysis is planned.

### Setting

This multicenter study will be conducted in hospital departments with a special focus on colonic and rectal surgery. Participating study sites are general and visceral surgery departments with at least one expert who has passed the German examination for specialization in proctology. The study is mainly performed within but not limited to the Helios clinic group. The majority of the participating study sites are hospitals for basic and standard care. Two study sites are maximum care hospitals. The Helios clinic group ensures uniform quality management and standardized documentation in the clinical file. For trial sites outside Helios, suitability for participation will be assessed before inclusion in the study. Study sites are located all over Germany. The number of study sites may be adjusted according to the frequency of patient recruitment.

In order to ensure the best possible transferability of the study results into the clinical routine, local clinical standards are applied, evaluated with regard to their influence on the results, and fully reported. Patients are provided with the best clinical standard.

